# Aims and objectives

The primary objective of this pilot RCT study is to:

1. To evaluate feasibility (cost and practicability) and acceptability of an early psychiatric intervention in a post-ICU clinic.

Secondary Objectives are:

1. Assess the impact of early psychiatric assessment and provision of referral options on self-efficacy and rates of health service access for patients requiring psychological intervention post-ICU
2. Measure the change in symptom severity for anxiety, depression, and PTSD between presentation, and 6 months after presentation.
3. Measure the impact on work, income, and independence in activities of daily living (ADL)

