**Participants and sample calculation:**

Data will be collected from a sample of approximately 30 patients attending the Redcliffe ICU follow-up clinic over a 12-month period, with 15 randomised to the control and intervention arms respectively.

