## Post Appointment Questionnaire

To address the primary outcome, the **Post Appointment Questionnaire** is an 8 item self-reported acceptability measure that has been specifically developed for this study. It has been adapted from similar surveys used in previous acceptability studies. Questions focus on whether the participant found their appointment helpful, how confident they feel about managing any psychological symptoms they have or may develop, and how optimistic they feel about their recovery.

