# Study procedure

Following verbal consent being provided, participants will be randomised to attend the clinic either when the psychiatrist is present or absent block randomisation in blocks of 4 or 6, in a 1:1 ratio, with the list generated by the study statistician (AB) and provided in enclosed envelopes to conceal allocation until verbal consent is provided. Full written consent will then be obtained when they attend their appointment.

Data will be collected with participant permission from their clinical records and medical history through a data request to ICU data collectors and hospital coders. These data will include demographics, frailty scores, diagnoses and severity of illness, previous mental health history, medications, multidisciplinary interventions, evidence of delirium during their admission and in-hospital complications.

| **Time points** | **Data collected** | |
| --- | --- | --- |
| Discharge from ICU | Contacted by clinical staff about the clinic. | |
| Clinic Appointment | Consent to participate, PICF completed. Routine Hospital Data accessed. Initial survey provided. Randomised to intervention or control arm. | |
|  | Control Group  Standard clinic cares provided as described below. | Intervention Group  Early psychiatric intervention provided as described below, in addition to standard clinic cares. |
| Intervention Follow-up |  | Participant contacted to evaluate response/tolerability of intervention. GP provided further advice as detailed below. |
| 6 Month Follow-up | Participant provides consent to continue participating and completes Follow-up Survey. | |

The timeframe of data collection is summarised in the table below:

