**Management of Anxiety Disorder**

Anxiety disorders will be managed according to the Royal Australian and New Zealand College of Psychiatrists guidelines[27]. A brief synopsis is provided below.

Mild Severity – Education provided for Cognitive Behavioural Therapy (CBT), and letter sent to GP to make referral.

Moderate Severity – Referral for CBT as above or Medication* or CBT plus Medication

Severe – CBT plus medication

*As per RANZCP Guidelines Selective Serotonin Reuptake Inhibitor (SSRI) or Serotonin and Noradrenaline Reuptake Inhibitor (SNRI) antidepressants will be offered as first line in consultation with patient’s preferences and comorbidities. Where these cannot be utilised, Mirtazapine will also be considered.

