**Management of Post-Traumatic Stress Disorder (PTSD)**

As with Anxiety disorders and Mood disorders, PTSD will be managed according to the respective Royal Australian and New Zealand College of Psychiatrists guidelines for PTSD, utilising a stepped care approach. A brief synopsis is provided below.

Psychological Treatments

Where indicated, education will be provided on Trauma Focused CBT (TF-CBT), and Eye Movement Desensitisation and Reprogramming (EMDR). Letter sent to GP to make referral for the agreed-on therapy.

Pharmacological Treatments

Pharmacological treatment will be discussed in circumstances where any of the following applies:

- The participant is unwilling or not in a position to engage in or access recommended psychological therapy.
- The participant has a comorbid condition or associated symptoms (e.g., clinically significant depression and high levels of dissociation) where SSRIs are indicated.
- The participant’s circumstances are not sufficiently stable to commence recommended psychological therapy (as a result, for example, of significant ongoing life stress such as domestic violence).
- The participant has not gained significant benefit from recommended psychological therapy.
- There is a significant wait time before psychological treatment is available.

First line medications considered will be SSRIs and SNRIs. Additional medications with evidence for PTSD such as Prazosin and Quetiapine will be considered where appropriate.

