**Intervention Follow-up**

The Psychiatrist will follow-up all patients where an intervention is initiated 4-6 weeks after their appointment. If there has been least partial clinical response, a letter will be sent to the participant’s GP recommending continuing current cares with ongoing monitoring. If there has been no response or a non-urgent deterioration, a letter will be sent to the GP suggesting referral for ongoing psychiatric review.

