## Statistical analysis

The demographics and results of the Baseline Outcome Measures Bundle will be described using proportions and associated 95% confidence intervals and compared between intervention and control groups to check the integrity of the randomisation.

Responses to the Post Appointment Questionnaire will be assumed to be additive and averaged to produce the primary outcome measure. Differences between groups will be assessed using t-test.

Changes in secondary outcome measures between baseline and 6 months will be compared between intervention and control groups to identify any clinically and statistically significant differences using ANCOVA regression with patients results at baseline fitted as a covariate. The model residuals will be checked to look for outliers and bi-modality. Leave-one-out sensitivity analyses will be used to look for patients that strongly influence the results.

Two-by-two tables will be created of the predicted and observed PICS, together with statistics on sensitivity, specificity, and negative and positive predictive value. Models will be checked for influential observations and outliers. The results will be reported using the EQUATOR TRIPOD checklist to ensure completeness and transparency[29].

The overall characteristics of the sample will be described using summary statistics. This will help inform the generalisability of our results. The number of patients approached and consented will be tabulated, together with the number who dropped out or died.

.

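### The intervention can start psychotropic drugs and is judged on acceptability, but the protocol describes no adverse-event recording in either arm and gives the 4-6 week tolerability check no outcome or analysis

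*Protocol*

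**What the plan says.** **Objective and primary outcome.** The primary objective (Aims and objectives) is: "To evaluate feasibility (cost and practicability) and acceptability of an early psychiatric intervention in a post-ICU clinic". Tolerability and harms are not named there. Acceptability is measured with an 8-item questionnaire developed for the study. Its section says: "Questions focus on whether the participant found their appointment helpful, how confident they feel about managing any psychological symptoms", and adds optimism about recovery. The Statistical analysis section states: "Responses to the Post Appointment Questionnaire will be assumed to be additive and averaged to produce the primary outcome measure", with a t-test between arms.

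**Drug treatment.** The sections on managing anxiety, mood disorder and PTSD allow the psychiatrist to start SSRIs, SNRIs, mirtazapine, tricyclics and several other agents, depending on diagnosis, severity and preference. For PTSD, for example: "Additional medications with evidence for PTSD such as Prazosin and Quetiapine will be considered where appropriate".

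**Tolerability contact.** The table under Study procedure has an intervention follow-up row that is filled only for the intervention group: "Participant contacted to evaluate response/tolerability of intervention". The control cell is empty. The Intervention Follow-up section gives the timing and the population: "The Psychiatrist will follow-up all patients where an intervention is initiated 4-6 weeks after their appointment". It then ties the GP letter to whether there was a response or a deterioration, and does not mention tolerability again. The Imminent risks section adds a second use of the call, which is to encourage urgent hospital review if such a risk is found.

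**Other information bearing on harm.** The Follow-up Survey repeats the PICS measures (HADS, PCL-5, EQ-5D-5L) in both arms at 6 months and adds the Health Services Use Questionnaire. The Statistical analysis section tabulates dropouts and deaths together with numbers approached and consented. Participant safety describes support contacts and redirection in acute deterioration, but no recording of events.

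**The concern.** The primary outcome rates the appointment and the participant's outlook. It is not described as covering what happened to people who then took a drug. The one contact that asks about tolerability appears in the table of data to be collected, but no recording method, variable, outcome or summary follows from it. It also reaches only intervention patients in whom something was initiated, so nothing learned there has a counterpart in the control arm.

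If the plan is followed as written, the pilot could report the intervention as acceptable without saying how many people began treatment, how many continued, how many stopped because they could not tolerate it, or how many had a serious event. Those are facts that the team planning the next trial would want. What to collect is settled in the protocol. A statistical analysis plan, which may exist here, can only summarise what was collected, and side effects not recorded at the time are hard to reconstruct later.

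**Working it through.** The Protocol gives no figure on harms, so there is nothing to reproduce. The check is first textual; the arithmetic after it is for scale only.

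**1. What each planned source can show, as described**

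| Source (Protocol section) | Arms | Could show | Side effects or stopping for intolerance described? |
|---|---|---|---|
| Post Appointment Questionnaire | Both | Helpfulness, confidence, optimism | No |
| 4-6 week contact (Study procedure; Intervention Follow-up; Imminent risks) | Intervention, where something was initiated | Response and tolerability | Asked, but with no recording, outcome or analysis |
| HADS, PCL-5, EQ-5D-5L at 6 months (Follow-up Survey) | Both | Worsening of symptoms or health status | No |
| Health Services Use Questionnaire (Follow-up Survey) | Both | Frequency and helpfulness of service attendance | No (items in Appendix 3, not shown) |
| Deaths and dropouts (Statistical analysis) | Not stated by arm | Participant flow | No cause stated |
| Participant safety; Imminent risks | Not a data source | Clinical redirection | No |

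Only one row touches tolerability. It covers one arm and leads to no analysis.

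**2. Can harm-related losses drop out of view?** Under Sampling and recruitment, if an intervention participant withdraws consent, the data already collected are removed. Under Exclusion criteria, consented participants without baseline or 6-month data are excluded. Someone who leaves because of side effects could therefore survive only as one unit in the dropout count.

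**3. Scale.** Input: "Data will be collected from a sample of approximately 30 patients attending the Redcliffe ICU follow-up clinic over a 12-month period", with 15 in each arm. Fifteen is a ceiling for the number started on a drug. Drugs are given on indication, mild anxiety leads to education and a GP letter, and a pre-existing illness already under care receives no further intervention. The Protocol does not say how many will be treated, so 5, 8 and 10 are assumptions to show the range.

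- Upper limit when no event is seen in n: one-sided 95% is 1 − 0.05^(1/n); two-sided 95% is 1 − 0.025^(1/n).
- Chance of seeing at least one event at true rate p: 1 − (1 − p)^n.

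| n | Upper limit, one-sided | Upper limit, two-sided | Chance of ≥1 event if p = 10% |
|---|---|---|---|
| 15 | 18.1% | 21.8% | 79.4% |
| 10 | 25.9% | 30.8% | 65.1% |
| 8 | 31.2% | 36.9% | 57.0% |
| 5 | 45.1% | 52.2% | 41.0% |

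With n = 15, the chance of at least one event is 53.7% for p = 5% and 96.5% for p = 20%.

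Two things follow. Zero events would not establish good tolerability at any of these sizes. A harm affecting one treated person in ten would nevertheless have about a 41% to 79% chance of appearing at least once, so recording is worthwhile even here.

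**The case against.** **Harm-related information is already collected.** A reader might infer that harms are not collected at all. The document does not support that. Deaths and dropouts are counted, symptom scales are repeated in both arms, and the tolerability contact stands in the table of data to be collected. Nor can one say that emergency attendance goes uncounted: the Health Services Use Questionnaire asks both arms about a range of services, and its items are in an appendix not shown. For the same reason, no one can state that the survey forms lack a side-effect item, only that none is described. This part of the objection stands, and it narrows the point to side effects, stopping for intolerance and serious events.

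**The call has more than one use.** It would be wrong to say that it serves only the GP letter, because it also triggers redirection for imminent risk. That is correct. Both uses are clinical, however, and neither turns the answer into study data.

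**This is an assessment and referral service, not a drug trial.** Drugs follow published guidelines and are given on indication, and 15 is only an upper bound. That is fair, and it limits the size of the matter. It does not remove it, because starting drugs remains part of what is being tested.

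**Acceptability by patient report is a legitimate choice, and tabulation can be left to the analysis plan.** Both are true. The primary outcome should not be redefined to include discontinuation. The collection itself is the gap, and an analysis plan cannot supply that afterwards.

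**Conclusion.** The point holds in a limited form. The intervention may start psychotropic drugs and acceptability is part of the primary objective, yet the Protocol describes no definition or systematic recording of adverse events in either arm. Tolerability is asked only of intervention patients in whom something was initiated, and it enters no objective, outcome or analysis. The existing both-arm measures may reveal worsening symptoms and some service use, but none is described as capturing side effects or stopping because of them.

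The size is modest. At most about 15 people could be treated, and probably fewer. Even 0/15 is compatible with a true rate of up to 18% (one-sided) or 22% (two-sided). The pilot therefore cannot demonstrate safety or tolerability, and any comparison between arms would be descriptive. This is something the sponsor should correct before recruitment, not a flaw that invalidates the design.

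The conclusion assumes that the appendix forms contain nothing on side effects beyond what the body of the Protocol describes. If they do contain such an item, the 6-month part of the fix is already met and what remains is the recording of the 4-6 week call and the reporting.

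**What to change.** 1. **Intervention Follow-up and the Study procedure table:** state that the 4-6 week call is recorded as study data on a short REDCap form covering treatment started, treatment continued, treatment stopped for intolerance, and any serious event. Define adverse and serious adverse events for this purpose.
2. **Follow-up Survey:** ask both arms one question on side effects and serious events at 6 months. Add emergency or hospital attendance only if the Health Services Use Questionnaire does not already cover it.
3. **Statistical analysis:** report the numbers with treatment started, continued and stopped for intolerance, and serious adverse events by arm, as counts with denominators. Present them beside the questionnaire-based acceptability outcome, without changing that outcome and without a hypothesis test.

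**Cost:** one short form and one survey item at contacts already planned, a few minutes per participant. The sample size, the primary outcome and every treatment rule stay as they are.

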## Standard Clinic Cares

As per the Standard Operating Procedure, patients attending the clinic participate in an interview, screening and assessment process followed by the opportunity to provide feedback. This is described in brief below. A comprehensive description can be found in Appendix 1.

**Conducting an Interview**

1. ICU admission reviewed to understand context, severity of illness and possible ailments.
2. Patient contacted through face to face, telehealth or telephone appointment.
3. Introduction and purpose of interview

Example: *“Thank you for coming in, the clinic runs to provide additional support to patients discharged from ICU. Research is being conducted to help us understand the impact our treatment is having on those surviving ICU admissions.”*

1. Gain confirmation to discuss admission details and conduct assessments.

Example: *“Do you recall your admission in ICU? Would you like me to explain what occurred?”*

If a patient declines and does not wish to talk about admission details, this is respected and staff move onto the assessment phase of the process.

1. Timeline of admission; from origin of admission to discharge. Key points and treatments received (i.e. Intubation, CPR, Medications received, OT, Extubation) are discussed.
2. Assessment form and standardised tools completed (see below):.

Routine Assessments

EQ-5D-5L

HADS

IES-R

Katz index of independence in activities of daily living

Montreal Cognitive Assessment / MOCA – BLIND

**Assessment**

History

- Electronic medical record and discharge summary reviewed.
- Events surrounding initial presentation used to begin the conversation about admission.
- ICU events such as issues and interventions encountered discussed.
- Staff are respectful of a patient's decision not to revisit their hospital admission in detail.

Assessment

- Assessment of body systems
- Patient asked to self-assess their quality of life and functional ability pre and post ICU
- Further assessment and referral to specialist services considered as appropriate.

Psycho- social

- Social history encompassing pre and post ICU admission
- Questions of relationships, employment, housing, and social interactions. Staff review services that may be able to alleviate additional stress.
- Patient's recollection of their admission explored, mindful that some patients will not remember anything about their time in ICU while others recall vivid memories.
- Acknowledging their feelings and experiences by explaining the prevalence and causes of hallucinations and delusions
- Staff consider possible referral for counselling services.

Feedback

- Review current processes.
- Explore services that may be required.

## Early Psychiatric Assessment and Referral Intervention

**General Assessment**

Participants randomised to the intervention group will attend the clinic on a day and time when the psychiatrist is in attendance. Consenting patients will see the psychiatrist after completing the standard clinical cares described above.

Prior to seeing the participant, the psychiatrist will review the clinical notes pertaining to their premorbid history, and their ICU admission. In addition, the psychiatrist will review the results of the baseline questionnaires, ICU notes and other relevant clinical information. The psychiatrist will discuss these results with the participant and explore how this information interrelates with their premorbid history, and their ICU experience.

The psychiatrist will conduct a comprehensive psychiatric review, including comorbid disorders, substance use, suicidal ideation, psychosocial stressors, social/emotional supports.

Diagnoses of any mental illnesses present will be made based on DSM-V criteria. Psychoeducation will be provided on any new mental illness present, with detail on how this interrelates with their critical illness recovery, and general lifestyle advice will be provided (exercise, healthy eating, sleep hygiene).

Initial treatment for any new mental illness commonly seen in post-ICU populations will be provided as described below.

**Management of Anxiety Disorder**

Anxiety disorders will be managed according to the Royal Australian and New Zealand College of Psychiatrists guidelines[27]. A brief synopsis is provided below.

Mild Severity – Education provided for Cognitive Behavioural Therapy (CBT), and letter sent to GP to make referral.

Moderate Severity – Referral for CBT as above or Medication* or CBT plus Medication

Severe – CBT plus medication

*As per RANZCP Guidelines Selective Serotonin Reuptake Inhibitor (SSRI) or Serotonin and Noradrenaline Reuptake Inhibitor (SNRI) antidepressants will be offered as first line in consultation with patient’s preferences and comorbidities. Where these cannot be utilised, Mirtazapine will also be considered.

**Management of Mood Disorder**

As with Anxiety disorders, Mood disorders will be managed according to the respective Royal Australian and New Zealand College of Psychiatrists guidelines for Mood Disorders[28]. A brief synopsis is provided below.

Psychological Treatments

Education will be provided on approved psychological treatments for mood disorders:

CBT, Interpersonal Therapy (IPT), Problem-Solving Therapy, Behavioral Activation Therapy, Nondirective Supportive Therapy, and Short-Term Psychodynamic Psychotherapy.

Pharmacological Treatments

Pharmacological treatment will be considered in context with the patient’s medical comorbidities, preferences and prominent mood symptoms. RANZCP guidelines are summarised in the table below.

| **Prominent Symptom(s)** | **Preferred Medication** |
| --- | --- |
| Anxiety | SSRI/SNRI |
| Cognitive Difficulties | Duloxetine, Vortioxetine |
| Sleep Disturbance | Mirtazapine, Agomelatine |
| Fatigue | Bupropion |
| Pain | Duloxetine, Tricyclic Antidepressant (TCA) |
| Melancholia | TCA |

**Management of Post-Traumatic Stress Disorder (PTSD)**

As with Anxiety disorders and Mood disorders, PTSD will be managed according to the respective Royal Australian and New Zealand College of Psychiatrists guidelines for PTSD, utilising a stepped care approach. A brief synopsis is provided below.

Psychological Treatments

Where indicated, education will be provided on Trauma Focused CBT (TF-CBT), and Eye Movement Desensitisation and Reprogramming (EMDR). Letter sent to GP to make referral for the agreed-on therapy.

Pharmacological Treatments

Pharmacological treatment will be discussed in circumstances where any of the following applies:

- The participant is unwilling or not in a position to engage in or access recommended psychological therapy.
- The participant has a comorbid condition or associated symptoms (e.g., clinically significant depression and high levels of dissociation) where SSRIs are indicated.
- The participant’s circumstances are not sufficiently stable to commence recommended psychological therapy (as a result, for example, of significant ongoing life stress such as domestic violence).
- The participant has not gained significant benefit from recommended psychological therapy.
- There is a significant wait time before psychological treatment is available.

First line medications considered will be SSRIs and SNRIs. Additional medications with evidence for PTSD such as Prazosin and Quetiapine will be considered where appropriate.

